**Statistical analyses and power analysis**

The estimated sample size is based on effect sizes reported in previous studies that have used BB-glasses as a treatment for sleep-disorders (20, 44). These studies showed strong effects on sleep quality in one group of healthy individuals and one group of persons diagnosed with ADHD. Because sleep problems during late pregnancy may have various hormonal and mechanical influences, we expect a medium effect size of about 0.5 (Cohens d) in the pregnant population. Setting the alpha to .05 (two-tailed), power set to .80, correlation between assessments at .50 reveals that 34 participants are needed minimum to detect statistically significant time (pre vs. post) x group (BB vs. control condition) interaction effects (45).

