**Study population and procedure**

A sample of 60 pregnant women will, during the standard control about gestational week 24, be recruited through consulting midwifes at antenatal-healthcare centers in the Municipality of Bergen. We will recruit until 60 participants have completed the protocol.

The inclusion criteria are; 1) healthy nulliparous women, 2) expecting one child, 3) being in the third trimester of a normal pregnancy, 4) not working at night during the study protocol, 5) able to wear an actigraph during the daytime and nighttime.

Exclusion criteria are; fever and other health conditions affecting sleep.

All participants will be given information about the study (oral and written form) by the consulting midwife. If the pregnant women consent to participate in the study, further information is provided by the research team. To exclude women with serious eye-condition affecting the translucency of the eyes, the red reflex of both eyes will be checked. The pregnant women will start going through the study protocol at gestational week 28. For baseline data, the participants will be assessed with subjective and objective measures for 7 days followed by 14 days of the BB-intervention/control-intervention. See Table 1. Consenting participants will be randomized (by www.randomizer.org) to either intervention/control condition.

Figure 1 Flow diagram of recruiting and data collection progress

|  | **Week 1 Day 1** | **Day 2–6** | **Day 7** |
| --- | --- | --- | --- |
| Morning  During the day  Evening | Actigraphy/light recorder  Sleep diary, incl. items about restless legs (RLS) , alcohol and physical activity  Demography  The Relationship Satisfaction Scale (RS)  Bergen Insomnia Scale (BIS)  The Epworth Sleepiness Scale (ESS)  The Beck Anxiety Inventory (BAI)  The Beck Depression Inventory (BDI-II)  Perceived Stress Scale (PSS)  The Penn State Questionnaire (PSWQ)  Karolinska Sleepiness Scale (KSS)  Positive and Negative Affect Schedule (PANAS)  Preesleep Arousal Scale (PSAS) | Actigraphy/light recorder  Sleep diary  PANAS  KSS  PSAS | Actigraphy/light recorder  Sleep diary  PANAS  KSS  PSAS  Melatonin sample from saliva |
|  | **Week 2 Day 8** | **Day 9-14** |  |
| Morning  During the day  Evening | Actigraphy/light recorder  Sleep diary  ESS  (PSS)  (PSWQ)  PANAS  KSS  PSAS  *Randomization: BB-glasses/control-glasses* | Actigraphy/light recorder  Sleep diary  PANAS  KSS  PSAS  *BB-glasses/control-glasses* |  |

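### The minimum of 34 women is the sample size for a 1.0 SD difference in change, not for d = 0.5; at d = 0.5 it gives about 29% power, and the planned 60 about 48%

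*Protocol*

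**What the plan says.** The section on statistical and power analysis in the Protocol cites strong effects of blue-blocking glasses in two earlier studies. It then scales the expectation down for pregnancy: "we expect a medium effect size of about 0.5 (Cohens d) in the pregnant population". The remaining inputs are "Setting the alpha to .05 (two-tailed"), "power set to .80" and "correlation between assessments at .50". From these it concludes that "34 participants are needed minimum to detect statistically significant time (pre vs. post) x group (BB vs. control condition) interaction effects".

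The section on study population and procedure sets the actual target: "We will recruit until 60 participants have completed the protocol". No power is stated for 60, and no other justification of the sample size is given. The allocation ratio is not stated either; the text says only that "Consenting participants will be randomized (by www.randomizer.org) to either intervention/control condition".

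**The concern.** A total of 34 is very small for a medium effect in a two-arm comparison, even with a baseline measurement. All the inputs and the result are given in the same paragraph, so the figure can be checked without an analysis plan.

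If the minimum is wrong, the 60 completers only appear to carry a wide margin over it. A reader told that 34 suffices for 80% power would take a null result from 60 women as good evidence against a medium effect. In fact the trial would miss such an effect about half the time.

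**Working it through.** **Inputs.** From the power paragraph: d = 0.5, two-sided alpha 0.05, target power 0.80, pre-post correlation ρ = 0.50, two groups and two times (m = 2), stated total N = 34. From the study population section: 60 completers. Assumed, because not stated: 1:1 allocation.

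**1. Reproducing 34.** The within-between interaction in repeated-measures ANOVA has noncentrality λ = f²·N·m/(1 − ρ) with 1 and N − 2 degrees of freedom. The usual two-group conversion is f = d/2 = 0.25.
- N = 34: λ = 0.0625 × 34 × 2 / 0.5 = 8.5, df (1, 32), power 80.7%.
- N = 32: power 78.1%.

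So 34 is the smallest even total with f = 0.25, which matches the protocol.

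**2. What f = 0.25 means for an interaction.** In a 2 × 2 layout, an interaction f of 0.25 means that each of the four cell means deviates by 0.25 SD, with alternating sign. The difference in change between arms is therefore 4 × 0.25 = 1.0 SD.

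The t-test on change gives the same answer. The SD of change is SD × √(2(1 − ρ)) = SD × √(2 × 0.5) = 1.0 SD. For a difference in change δ, in SD units, λ = δ²·N/(4 × 2(1 − ρ)), which at N = 34 is 8.5·δ². Setting this equal to 8.5 gives δ = 1.0. A t-test on change with d = 1.0 returns the same N = 34 and the same 80.7%.

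**3. The stated effect.** A difference in change of 0.5 SD is f = 0.5/4 = 0.125. Because the SD of change equals the raw SD at ρ = .50, it does not matter which of the two standardises d.

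| Total N | λ = 0.25·N/4 | Power at d = 0.5 |
|---|---|---|
| 34 | 2.125 | 29.3% |
| 60 | 3.75 | 47.8% |
| 126 | 7.875 | 79.5% |
| 128 | 8.0 | 80.1% |

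The required total is 128, which is 128/34 = 3.8 times the stated figure. At N = 60, 80% power is reached at a difference of 0.74 SD.

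**4. Could another reading of d = 0.5 give 34?**

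| Variant | Power at 34 | Power at 60 | N for 80% |
|---|---|---|---|
| Baseline-adjusted (residual variance 1 − ρ² = 0.75) | 37% | 59% | 98 |
| One-sided test | 41% | 61% | 102 |

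- With baseline adjustment, the difference detectable with 80% power at N = 60 is 0.64 SD.
- Reading 34 as per arm (68 in total) gives 53%.
- A paired pre-post t-test in a single group, with a mean change of 0.5 SDs of change, also first reaches 80% at n = 34 (80.8%; n = 33 gives 79.5%). It has no control arm and is not the interaction.

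**5. Sensitivity to the correlation** (change-score test, difference 0.5 raw SD):

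| ρ | Power at 34 | Power at 60 |
|---|---|---|
| 0.3 | 22% | 36% |
| 0.5 | 29% | 48% |
| 0.7 | 45% | 69% |
| 0.8 | 61% | 85% |

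**The case against.** The protocol does not define d. It could be a within-group change or a difference at post-test, and the metric of the earlier studies' effects cannot be checked here. That is a fair criticism of the text, but it does not rescue 34. The sentence attaches the effect to the group-by-time interaction, so a between-arm difference is the natural reading. For 34 to be right, the arms would have to differ in change by 1.0 SD, for instance by moving 0.5 SD in opposite directions. Nothing says so, and the control glasses are described as having no blue-blocking effect.

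The route to 34 is also not unique, since a one-group paired test gives the same number. The cause of the error is therefore inferred, not proven. Neither route yields the sample size for the test that is named.

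The protocol attaches 80% power to 34 and never states a power for 60. That is literally true, but a minimum of 34 for 80% implies at least 80% at 60.

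The strongest point concerns the correlation. Several outcomes are recorded daily, and averages over a week may correlate above .50; at 0.8, 60 women would give 85% by the change-score test. This stands as a caveat. However, .50 is the protocol's own input. Melatonin onset, the insomnia scale and the anxiety and depression inventories are scheduled once at baseline and once at the end, so averaging over days does not help them.

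**Conclusion.** The concern holds. Under the protocol's own inputs and 1:1 allocation, 34 women give 29% power for a between-arm difference of 0.5 SD in change. The planned 60 completers give 48%, and 128 are needed for 80%. Baseline adjustment raises the figure at 60 to 59%, which is still short, and would need 98 women.

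The shortfall is at the effect the protocol says it expects; for a 1.0 SD difference, 60 women give 97% power. The conclusion rests on reading d as the between-arm difference in change and on the stated correlation of .50. Because 34 is the only sample-size justification in the document, it has to be corrected.

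**What to change.** Delete the 34, state that d is the between-arm difference in change in SD units, and give the allocation ratio. If 60 is kept, wording such as the following would serve:

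*For a between-group difference of 0.5 SD (correlation .50, two-sided alpha .05, equal allocation), 60 women give 48% power for the time-by-group interaction and 59% with adjustment for baseline; 80% power is reached for differences of about 0.74 SD and 0.64 SD respectively. A non-significant result does not exclude a medium effect.*

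The 59% and 0.64 SD belong in the text only if baseline adjustment is the planned analysis. If the sponsor expects a higher correlation for outcomes averaged over days, that value should be stated and justified for each outcome.

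Keeping 60 costs a few sentences in the protocol and in anything that repeats the figure, with no extra participants; the stated power becomes less favourable. The alternative is to enlarge the trial to 128 completers, or 98 with baseline adjustment, to deliver 80% power at d = 0.5.

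### The only treatment test named is a pre-post by group interaction; adjusting for the pre-randomisation baseline would be more precise at almost no cost

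*Protocol*

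**What the plan says.** The section Statistical analyses and power analysis sizes the trial to detect "time (pre vs. post) x group (BB vs. control condition) interaction effects". The inputs are "Setting the alpha to .05 (two-tailed), power set to .80, correlation between assessments at .50" and an effect given as "we expect a medium effect size of about 0.5 (Cohens d) in the pregnant population". The result is that "34 participants are needed minimum to detect statistically significant" effects of that kind. No other test of the treatment effect is named in the protocol, and no analysis that conditions on baseline is mentioned.

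Under Study population and procedure, "the participants will be assessed with subjective and objective measures for 7 days followed by 14 days of the BB-intervention/control-intervention". The Day 8 column of Table 1 carries the entry "Randomization: BB-glasses/control-glasses", after the baseline week. The same section plans to recruit until 60 women have completed the protocol.

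Table 1 gives two kinds of outcome:

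- **Measured once before and once after:** salivary melatonin for DLMO (Days 7 and 21), and BIS, BAI and BDI-II (Days 1 and 21).
- **Measured daily:** sleep diary, actigraphy, PANAS, KSS and PSAS.

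**The concern.** In a randomised trial with a baseline taken before allocation, three comparisons estimate the same treatment effect: post values alone, change from baseline, and post values adjusted for baseline. They differ in precision. The change score in effect fixes the baseline slope at 1. Adjustment estimates the slope from the data and, in large samples, is never less precise. The protocol builds its sample size on the change-score version and assumes a correlation at which that version is no more precise than ignoring a single baseline measurement.

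What is at stake is precision in a trial of 60 women, with data that will be collected anyway. DLMO, anxiety and depression carry much of hypotheses 2 and 3, and they are the outcomes for which the loss is largest.

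**Working it through.** **Inputs.** From the Protocol: two-sided alpha .05, power .80, d = 0.5, correlation ρ = .50 and minimum N = 34 (Statistical analyses and power analysis); 60 completers (Study population and procedure). Assumed: 1:1 allocation, which is not stated, and equal SD before and after.

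**1. Reproduce N = 34.** The cited software's routine for a within-between interaction uses λ = f²·N·m/(1−ρ), with m = 2 measurements and N−2 denominator df. With f = 0.25 and N = 34, λ = 0.0625 × 34 × 2 / 0.5 = 8.5 and power is 0.807. N = 32 gives 0.781. The stated figure is reproduced.

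**2. What effect N = 34 represents.** With two time points the interaction F test is the square of the t test on change scores, so λ = δ²·N/(4V), where δ is the between-group difference in change in SD units and V = 2(1−ρ) = 1.00. Setting δ² × 34/4 = 8.5 gives δ = 1.0 SD.

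**3. Variance per participant, in SD² units.**

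- Post value only: 1.00
- Change score: 2(1−ρ) = 2 × 0.5 = 1.00
- Baseline-adjusted: 1−ρ² = 1 − 0.25 = 0.75

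The ratio of adjusted to change-score variance is (1+ρ)/2 = 0.75, a 25% loss. Over other correlations the loss is 35% at .3, 20% at .6, 15% at .7, 10% at .8 and 5% at .9. A simulation of 20,000 trials at ρ = .50 gave ratios of 0.76 at N = 60 and 0.78 at N = 34. The small excess over 0.75 is the cost of estimating the slope.

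**4. Outcomes averaged over nights.** Suppose any two daily values correlate r (assumption: the same r for all pairs of days). The 7-night baseline mean has variance (1+6r)/7, the 14-night mean has (1+13r)/14, and their covariance is r.

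| r | corr. of means | change-score variance | adjusted variance | loss |
|---|---|---|---|---|
| .3 | .80 | 0.40 + 0.35 − 0.60 = 0.150 | 0.35 − 0.09/0.40 = 0.125 | 17% |
| .5 | .90 | 0.571 + 0.536 − 1.00 = 0.107 | 0.536 − 0.25/0.571 = 0.098 | 8% |
| .6 | .93 | 0.657 + 0.629 − 1.20 = 0.086 | 0.629 − 0.36/0.657 = 0.081 | 6% |

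**5. Power and sample size at ρ = .50, one value before and one after** (noncentral t, df N−2 for change and N−3 for adjusted).

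| | Change score | Adjusted |
|---|---|---|
| δ = 0.5 SD: power at N = 60 | 47.8% | 59.4% |
| δ = 0.5 SD: N for 80% power | 128 | 98 |
| Effect detectable at N = 60 with 80% power | 0.74 SD | 0.64 SD |
| δ = 1.0 SD: power at N = 60 | 96.8% | 99.3% |
| δ = 1.0 SD: N for 80% power | 34 | 26 |

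For δ = 0.5 SD at N = 60, power goes from 36.3% to 51.4% at ρ = .3 and from 69.1% to 76.0% at ρ = .7.

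**The case against.** Four points can be made against the concern.

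- **The test appears in a sample-size sentence, and a SAP that is not shown may adjust for baseline.** This is a fair caution. But the interaction is the only test named under a heading that covers the analyses, and N = 34 is derived from it. If a SAP uses another estimator, the protocol still describes and sizes a different one.
- **The interaction is conventional and valid.** This stands in full. A reader might infer that the planned test is biased or ignores chance baseline imbalance. It is not biased, and it does subtract baseline. The issue is efficiency alone.
- **A quarter is too large for the nightly outcomes.** This also stands. A reader might apply the 25% to every outcome, but it belongs to single before and after values at ρ = .50. For nightly means the change score already removes most of the between-woman variance: at r = .3 the post-only variance is 0.35, against 0.15 for change and 0.125 for adjustment.
- **The power gain depends on how d is read.** This stands too. The effect that N = 34 represents already has about 97% power at 60, so the rise from 48% to 59% applies only if d = 0.5 means a 0.5 SD difference in change.

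A reader might also infer from Table 1 that the Day 8 diary puts an untreated night into the treated period, or that the last treated night goes unrecorded. The document does not support this. The table's morning, day and evening rows are merged in the text at hand, and the protocol nowhere says which night belongs to which Day. Counting nights by the evening on which they begin gives exactly 7 and 14.

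**Conclusion.** The point holds as a matter of precision. At the protocol's own correlation, the named test loses 25% of the information on outcomes taken once before and once after. For nightly means the loss is about 6% to 17%, if daily values correlate .3 to .6 with equal correlation between days. The direction does not depend on the correlation: (1+ρ)/2 is below 1 for every ρ below 1. In the simulation at N = 60, estimating the slope cost about 1.6% (0.762/0.75), well inside the gain over the range considered.

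Adjustment does not rescue the sample size. If d = 0.5 is a between-group difference in change, 60 completers give 59% power at ρ = .50 even after adjustment, and 98 would be needed for 80%. How the effect size was entered in the calculation is a separate question.

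**What to change.** State in Statistical analyses and power analysis that the treatment effect is estimated by ANCOVA, or by a linear mixed model for repeated nightly outcomes, with the pre-randomisation value of the same outcome as covariate and treatment group as the effect of interest. Use the baseline-week mean for daily measures and the single baseline value for measures taken once (DLMO, BIS, BAI, BDI-II). Restate the sample-size calculation for that analysis, giving the effect as a between-group difference in SD units.

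The cost is one sentence of analysis wording, a matching line in the calculation and one degree of freedom. No visit, instrument or additional participant is required by the change of analysis.

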**Ethical considerations**

All participation will be based on written consent and volunteerism. There are no known side-effects, except of transient headache reported in 5-10 by wearing the blue-blocking glasses. The trial will apply the Regional Ethical Comity for approval to conducting the study. The trial will be registered in the ClinicalTrials.gov database.

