**Blue blocking glasses as a safe intervention**

Recent studies have shown that use of blue-blocking glasses (BB-glasses) in the evening improve sleep quality (subjectively reported) among persons with insomnia, and prevent alertness caused by blue-light emitting screens such as smartphones and iPad (19, 20). The mechanisms behind involves specialized retina ganglion-cells (intrinsically photoresponsive Retinal Ganglion-Cells, IpRGC), responsible for detecting and conveying the circadian day light signal directly to the SCN. IpRGC respond to a narrow band of wavelengths, most sensitive to the frequencies between 446 and 484 nm; the blue light (21, 22). Amber/orange tinted glasses works as a filter by blocking wavelengths shorter than 530 nm and have been shown to preserve normal nocturnal melatonin levels in a light environment that otherwise completely suppresses the natural production of melatonin (23). “Virtual darkness” to the SCN is therefore achievable by blocking the blue wavelengths of light (24, 25). The use of BB-glasses in evening/night allows the melatonin-production to follow the natural cycle of light and darkness, even when electric light and light-sources such as smart-phones, iPad and TV are used. In a recent case study, we have demonstrated that sleep is rapidly transformed from very irregular to markedly regular during the use of BB-glasses (26). Importantly, blocking blue light during the evening and night is not reported to produce any harmful side-effects, and in contrast to medication it does not depend on detoxification processes in the liver. Treatment studies show that use of BB-glasses are effective in improving mood, as those wearing BB-glasses recovered more quickly for postpartum depression (19).

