**Aims**

The main aim of this project is to investigate the effect of BB-glasses used in the evening and night on Dim Light Melatonin Onset (DLMO), alertness (subjectively), sleep quality (subjectively and objectively), positive and negative affect and mood for pregnant women in the third trimester. Furthermore, we want to establish the prevalence of sleep disturbance, sleep-pattern and sleep-related behavior in the study population, and the association with daily/nightly light exposure.

The sub goals are:

1. To assess the light environment and sleep-pattern among pregnant women in the beginning of the third trimester.
2. To investigate the effect of blue-blocking glasses on sleep quality among pregnant women in the beginning of the third trimester.
3. To investigate the effect of blue-blocking glasses, in the evening and during the night, on DLMO, positive and negative affect and symptoms of anxiety and depression among pregnant women in the beginning of the third trimester.

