**Intervention**

The intervention comprises blue-blocking glasses (orange-tinted), which remove more than 90% of the blue wavelengths; wavelengths shorter than 530 nm. (26) The control-glasses will be light grey, with no blue-blocking effect.

The intervention group and control group will be instructed to wear the BB-glasses/control glasses from two hours before normal bedtime at night, until they go to bed. They will be informed to not expose themselves for light without wearing the BB-glasses during the night, and if needed, like going to the bathroom during night, to wear the BB glasses.

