**Instruments/Measures**

*Actigraphy* (29). For indirect measure of sleep patterns, we will use a commercially available actigraph (Actiwatch Spectrum from Philips Respironics). This actigraph looks like a watch and is constructed to register motor activity. It is worn around the wrist and registers movements by a piezo-electric accelerometer. Motor activity for periods of thirty seconds will be recorded. Data can be converted to objective sleep parameters. Actigraphy has shown to be sufficiently sensitive to detect changes in sleep length (30).

*Light recorder* (29). The actigraph Actiwatch is also constructed to register light; total white light, blue, green and red light.

*Melatonin samples* from saliva for establishing DLMO on day 7 during baseline-week, and repeated the last evening of the consecutive intervention-week day 21.

*Sleep diary* (31). Daily subjective estimates of bedtime, rise-time, sleep latency, number of awakenings, wake time after sleep onset, final awakening time, rise time, total sleep time, sleep efficiency, sleep quality and daytime functioning.

*Pregnancy related complaints* during the night will be daily measured by self-reporting of itching of the skin, leg cramps, restless legs, pelvic pain, back pain, fetal movements, nausea, vomiting, reflux and nocturia. The response scale range from 1 (no complains) to 5 (extremely).

*Restless Legs* (RLS) (32) will be assessed using the diagnostic criteria from the International Classification of Sleep Disorders – third edition.

*Physical activity* (33) will be daily measured by asking “How many minutes were you physical active, which was enough to raise your breathing rate?” Participants will be asked to fill in the amount of minutes every day.

*Alcohol consumption* will be measured as daily subjective estimates by asking “Did you drink alcohol yesterday, and how many alcoholic drinks?” by responding 0 for no alcohol, or specify the number of alcoholic drinks.

*The Bergen Insomnia Scale (BIS)*(34). The BIS assesses symptoms of insomnia during the previous week, and are related to sleep onset, maintenance, early morning wakening insomnia, not feeling adequately rested, experiencing daytime impairment and being dissatisfied with current sleep. The response alternatives range from 0 (no days per week) to 7 (all days per week).

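### The protocol names transient headache as the only known side effect of the glasses, but no measure it describes records headache, so the trial as described yields no headache data by arm

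*Protocol*

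**What the plan says.** The protocol's Ethical considerations section names one side effect: "There are no known side-effects, except of transient headache reported in 5-10 by wearing the blue-blocking glasses". The figure carries no unit. The background section titled "Blue blocking glasses as a safe intervention" says that "blocking blue light during the evening and night is not reported to produce any harmful side-effects".

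Under Instruments/Measures, pregnancy-related complaints "during the night will be daily measured by self-reporting of" a fixed list: "itching of the skin, leg cramps, restless legs, pelvic pain, back pain, fetal movements, nausea, vomiting, reflux and nocturia". Each is scored from 1 to 5. Headache is not on the list. The descriptions of the other instruments and the schedule in Table 1 do not mention headache, adverse events, tolerability or reasons for stopping.

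The Intervention section has the glasses worn "from two hours before normal bedtime at night, until they go to bed", and again if the woman gets up to light during the night. Study population and procedure says that recruitment continues until 60 women have completed.

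**The concern.** Every woman is asked daily about ten complaints, but not about the one effect that the protocol itself attributes to the glasses. What the diary asks is a matter of data collection. If the question is not put while the women wear the glasses, no analysis plan can recover the answer.

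The rule of recruiting to 60 completers adds to the gap. A woman who stops early is in effect replaced. Since no record of reasons for stopping is described, a withdrawal because of headache could leave no mark in the data.

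At stake is descriptive harm information in pregnant women, in a project whose rationale leans on the glasses being safe. Headache might also bear on sleep and mood ratings. The protocol gives nothing from which to size such an effect, so this is a reason to record headache and not evidence of bias.

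**Working it through.** **Is headache captured anywhere?**

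- Ethical considerations: headache is the only side effect named.
- Daily complaint list: itching, leg cramps, restless legs, pelvic pain, back pain, fetal movements, nausea, vomiting, reflux, nocturia. That is ten items, none of them headache.
- Other measures described: actigraphy and light, melatonin, sleep diary, restless legs, physical activity, alcohol, BIS, KSS, PANAS, PSAS, ESS, BAI, BDI-II, PSWQ, PSS, relationship satisfaction, sociodemographics. None is described as recording headache or tolerability.
- Table 1, Days 1 to 21: no entry for adverse events or reasons for stopping.

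**Would adding headache to the existing list be enough?** The list asks about the night, whereas wear begins two hours before bedtime. A transient headache in the evening could fall outside a night-time question, so the wording of the item matters.

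**What could the item show?** The protocol offers no figure on this point apart from 5-10, and its sample-size calculation does not concern harms. Inputs:

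- 60 completers (Study population and procedure); 30 per arm, assuming 1:1 because no ratio is stated.
- Rate p of 0.05 to 0.10, assuming that 5-10 means percent.

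Expected cases in the active arm, n × p:

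- 30 × 0.05 = 1.5
- 30 × 0.10 = 3.0

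Chance of at least one case, 1 − (1 − p)^n:

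- 1 − 0.95^30 = 0.785
- 1 − 0.90^30 = 0.958

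Power of Fisher's exact test, two-sided 0.05, 30 per arm, no cases in the control arm:

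- 5 v 0 gives p = 2 × C(30,5)/C(60,5) = 0.052, not significant.
- 6 v 0 gives p = 2 × C(30,6)/C(60,6) = 0.024, significant.
- Power is therefore P(X ≥ 6), which is 0.003 at 5% and 0.073 at 10%.
- With background headache in the control arm, power falls further: for 10% in the active arm it is 0.043 against 2% and 0.019 against 5%.

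Exact two-sided 95% upper limit when 0 of 30 report headache: 1 − 0.025^(1/30) = 0.116, or 11.6%. Zero cases would thus not exclude even the top of the protocol's own range, if that is 10%.

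So the item would probably pick up one or more cases and allow a description by arm. It could not support a comparative test or a safety conclusion.

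**The case against.** A reader might infer that leaving headache out is what prevents the trial from supporting its claim of a safe intervention in pregnancy. The protocol does not bear that out. Safety is a premise in the background, resting on earlier reports. The main aim begins "The main aim of this project is to investigate the effect of BB-glasses used in the evening and night on Dim Light Melatonin Onset" and goes on to alertness, sleep, affect and mood. None of the three planned original papers has safety as its topic, and only the title of the lay article raises safe treatments, as a question. With 60 women the trial could not establish safety even with the item. This objection stands.

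It is also fair to say that the list is meant for pregnancy complaints at night and is not a side-effect checklist, so the omission does not contradict its purpose. The gap is that nothing else described does the job either.

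A reader might also see a plain contradiction between the background and the ethics section. That is too strong: a transient headache need not count as harmful, so the two statements can be read together. The missing unit is editorial and affects no design figure.

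Finally, silence is not proof. Some pages, the consent material among them, are not in the text at hand, and individual questionnaire items are not printed. The point is therefore limited to what the protocol describes. None of this answers the core: the one named side effect has no described place in the data collection. Low power is a reason not to test the difference, but not a reason to leave it unrecorded.

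**Conclusion.** The point holds in a limited form. As described, the trial will produce no headache or tolerability data by arm, although headache is the only side effect it names, and women who stop because of headache could go unrecorded. No planned efficacy result is shown to be affected.

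The size is modest: 1.5 to 3 expected cases in the active arm and a 79% to 96% chance of at least one. These figures rest on two assumptions, percent as the unit and 30 women per arm. They also take the quoted range as the rate in this population and leave aside background headache, which would raise the counts in both arms. The change is worth making because it costs almost nothing and cannot be made after data collection.

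**What to change.** - Add one daily headache item on the same 1-5 scale, in both arms from Day 1, worded to cover the evening wear period as well as the night. Starting on Day 1 gives a seven-day baseline against which to read the 14 days of wear.
- Record the reason whenever a woman stops the glasses or leaves the study, including those replaced under the 60-completer rule.
- Report both descriptively by arm, with no hypothesis test and no safety claim.
- As a minor edit, supply the unit for 5-10 in Ethical considerations, and align that sentence with the background statement on side effects, for instance by saying whether transient headache is counted as harmful.

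The cost is one extra diary question per day, a short field for reasons for stopping, and a few table rows.
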